### Other secondary outcomes

#### Neurodevelopment assessment of infants

In order to assess the impact of maternal interventions on early childhood development (ECD) as growth trajectory, four different approaches or tools will be used to determine the changes at 6 and 12 months of age. This will be undertaken by a team of psychologist and trained senior research staff.

##### Early learning and motor ability

The “Mullen Scales of Early Learning” will serve as a compass for assessing cognitive and motor ability of each infant. The scale will use gross motor, visual reception, fine motor, expressive language, and receptive language to score target strengths and weaknesses among the infants, with each module having specific skip patterns to follow according to age group. The module for infants less than 12 months of age usually takes 25–35 min to complete. This examination will be performed on all eligible infants.

##### Neurological examination

The “Hammersmith Infant Neurological Examination (HINE)” will be used for the neurological examination of infants. It consists of six subscales (tone, tone patterns, reflexes, spontaneous movements, abnormal neurological signs, and behavior) and a total score. There are 34 items, with a maximum possible score of one per item, the points of which are totaled to provide an overall optimality score, as well as the six subscale scores. This will be performed on all eligible infants.

##### Global Scale for Early Development

The Global Scale for Early Development (GSED) aims to fill the neurological and biopsychosocial gap that may present in infancy and childhood through the development of two internationally standardized and validated measurement instruments for the assessment of ECD in children under 3 years of age at population (short form) and programmatic (long form) levels. The instruments are being developed by a multidisciplinary team led by the World Health Organization. Both GSED instruments are constructed from a common item bank (see box for detailed methodology). The first is a short, caregiver-report instrument intended for population-level measurement to assess and map child development status, draw attention to populations in most need of support, track trajectories of child development over time at a population level, and monitor benefits of national-level policies and programming. The second is a longer instrument for program evaluation that combines direct assessment and caregiver report to quantify the impact of an intervention on early developmental outcomes. Both forms are developed to be culturally neutral, easy to administer; open-access and freely available; acceptable and understandable to caregivers and children; and easily interpretable by policymakers and program personnel. The instruments are designed to be holistic measures for interpretation at the population or group level. They are not intended for individual diagnosis or screening of children. The data collected via GSED will provide the conceptual and empirical basis for the future development of “norms” that can be used to monitor the proportion of children who are developmentally on track [31].

##### Brain morphology

On a sub-sample of 50 infants per arm, brain imaging will be performed using magnetic resonance imaging (MRI) to assess brain volumes and morphometry. The portable low-field scanner, “Hyperfine MRI machine” will be used for this purpose. Approved by the Food and Drug Authority (FDA) [32], this new diagnostic tool will be used to assess brain development in complement to other ECD assessments mentioned above.

#### Participant experience and rating different characteristics of BEP product

At weeks 19 and 32 of gestation, the participants in the intervention arms will be approached to share their product experience with BEP supplements. This will include product taste, odor, texture, physical appearance, and packaging.

#### Maternal depression

##### Antenatal period

Pregnant women will be screened for depression at weeks 19 and 32 of pregnancy by a team of one psychologist and trained senior research using the “Patient Health Questionnaire 9-item tool (PHQ9)” will be used to screen the. In subject(s) requiring urgent care based on the finding, a referral for higher-level care will be furnished for further diagnosis and treatment.

##### Post-partum period

Using Edinburgh Postnatal Depression Scale (EPDS) tool, data on maternal depression at 6 and 12 months post-partum will be collected by the same team of one psychologist and trained senior research staff. In a case where participant(s) require urgent care based on the finding, a referral for higher-level care will be furnished for further diagnosis and treatment.

#### Biomarker assessment during pregnancy period

##### Maternal blood specimen collection

Maternal blood will be collected at enrollment and 32 weeks of pregnancy from all consensual participants to assess the levels and differences of hemoglobin (g/dl), ferritin (ng/ml), and vitamin D (ng/ml) from each arm. Separate blood specimens for metabolomic analyses will be simultaneously drawn using the “Volumetric Absorptive Microsampling” (VAM) technique.

On a sub-sample of 50 pregnant women per arm approached via convenience sampling, plasma for Niacin metabolites and for niacin co-enzymes, specifically erythrocyte nicotinamide adenine dinucleotide (NAD) and nicotinamide adenine dinucleotide phosphate (NADP), will also be collected at the same time point to compare the levels of these metabolites among the four arms with those receiving an extra daily dose. On this same sub-sample, plasma for proteomic analysis will be collected at 19 and 32 weeks of pregnancy to gain an in-depth analysis of proteome and assess the potential impact of administrating azithromycin.

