## Methods

### Trial design

This is a multi-arm community-based randomized controlled, open-label, assessor-blinded superiority trial with a treatment allocation ratio of 1:1:1:1. A multi-arm trial was selected to determine the incremental impact of BEP to the pregnant woman, along with two doses of oral azithromycin or oral daily nicotinamide and choline on birth weight. This protocol has been developed in accordance with the guidelines set forth by Standard Protocol Items: Recommendations for Interventional Trials (SPIRIT) [26].

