### Randomization and allocation concealment

After written informed consent is obtained, randomization will be performed by the team. Stratified block randomization with blocks of sizes 4, 8, and 12 will be used. Sequence generation will be performed by an independent statistician using a random selection method before the beginning of the trial. Self-adhesive, pre-coded sticky labels with unique identification numbers will be applied to sealed opaque envelopes containing the coded randomization identification number and intervention name to ensure that the randomization process and allocation are blinded. Baseline information regarding nutrition and exclusive breastfeeding will be recorded. Anthropometric measurements of both the mother and newborn will be performed, and follow-up procedures will be explained. Figure 1 shows the trial processes in detail.

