### Blinding

The outcome assessors, responsible only for the anthropometry measurements, will be blinded and assigned a schedule that does not overlap with those of the follow-up teams. All investigators will also be blinded to group allocation throughout the period of the study. Moreover, an interim analysis on the blinded arms will be executed by an independent statistician for the Data Safety and Monitoring Board (DSMB). Furthermore, the data analyst performing the final analysis will also be blinded, and the code will eventually be revealed after the blinded results will be shared with DSMB and investigators in a final review meeting.

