**Infant’s growth and neurodevelopment assessment**											
*Monthly infant and maternal anthropometry measurements performed by separate team (blinded from intervention details)*											×
*Neurodevelopment assessment using Mullen, HINE and GSED – at 6 and 12 months of infant’s age plus maternal depression* ^*l*^											×
*MRI scan of infants* ^*k*^											

^a^Window period for eligibility assessment and enrollment is 8–18.9 weeks of gestation

^b^Initial 1–13 days from enrollment

^c^15–25 days from enrollment

^d^29–38 days from enrollment

^e^Pre- and post-Azithromycin administration, i.e., at weeks 20 and 28 of gestation

^f^48 days from enrollment

^g^Only in intervention arm

^h^Only in intervention arm C and window period of 7 days

^i^Only monthly basis

^j^All participants who agreed

^k^Sub-sample of 50 in each arm

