##### Blood specimen collection

From the same 50 mother-infant dyads per arm, infantile blood specimens will also be simultaneously collected at 1–2, 3–4, 5–6, and 12 months of infantile age for metabolomic work using Volumetric Absorptive Microsampling (VAM). The specimens will be stored in − 80 °C freezers at the IDRL and NRL storage areas of the Aga Khan University for further analysis in future research for an indefinite time. The samples will be color-coded by the type of specimen as part of a unique identification system and de-identified with barcodes, specific IDs for different time points, and mother-infant dyad information. All the ethical aspects pertaining to the storage of these samples have been approved by the Ethics Review Committee at the Aga Khan University.

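### The 50-per-arm specimen sub-sample is chosen by convenience in an open-label trial, so randomisation no longer guarantees comparable arms in those sub-studies

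*Protocol article*

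**What the plan says.** The section on maternal blood specimens states the selection method: "On a sub-sample of 50 pregnant women per arm approached via convenience sampling". The niacin work is meant "to compare the levels of these metabolites among the four arms with those receiving an extra daily dose", and the proteomic work in the same women is meant to show what azithromycin does. The sections that follow take urine, pregnancy stool, cord blood and colostrum from the same women. The dyad stool and infant blood sections continue with them, the latter "From the same 50 mother-infant dyads per arm". In Table 2, footnote k sets the number as "Sub-sample of 50 in each arm".

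On masking, Trial design says: "This is a multi-arm community-based randomized controlled, open-label, assessor-blinded superiority trial with a treatment allocation ratio of 1:1:1:1". The Blinding section says: "The outcome assessors, responsible only for the anthropometry measurements, will be blinded". It also blinds investigators and the final analyst, but does not mention recruitment to the sub-sample. On timing, the randomisation section says: "After written informed consent is obtained, randomization will be performed by the team". Under Strengths and limitations, the countermeasures to selection bias are an independently generated sequence and blocking.

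**The concern.** Random allocation makes the arms comparable as whole groups. A subset keeps that property if it is drawn at random, or if entry to it cannot depend on the arm. Convenience selection secures neither. The listed countermeasures protect entry to the trial, not later entry to the sub-sample.

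An arm-related filter is plausible here. The Follow-ups section has the follow-up teams delivering the supplements. In Table 2, supplement compliance is assessed only in the intervention arms, and one set of daily visits is tied to azithromycin dosing. Who is easy to approach, or willing to give specimens, could therefore differ by arm. The Discussion presents the nested sub-studies as evidence on mechanism. A metabolite, milk or microbiome difference between arms could then partly reflect who was picked.

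**Working it through.** The article gives no calculation for 50 per arm, so there is no figure of the plan's own to reproduce. The check has three parts.

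**1. Is entry to the sub-sample shown to be independent of arm?**
- The method is convenience (Maternal blood specimen collection).
- The quota is by arm (Table 2, footnote k), so the arm has to be known when places are filled.
- Allocation directly follows consent, at 8 to 18.9 weeks. Proteomic plasma and stool begin at week 19.
- Blinded assessors cover anthropometry only.
- No random draw, masked approach or selection before allocation is described.

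Independence is therefore not secured. That the arm was known at selection is an inference, though a strong one.

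**2. How much room is there, and what would a shift do?**
- Fraction chosen: 50/471 = 10.6% of an arm (Sample size section), or 50/459 = 10.9% using the abstract's total, since 1836/4 = 459.
- Standard error of a difference between two arms of 50, in SD units: sqrt(2/50) = 0.20.
- Detectable difference at 80% power, two-sided 5%: (1.96 + 0.84) × 0.20 = 0.56 SD.
- With no true effect and a selection shift of b SD, the rejection probability is 1 − Φ(1.96 − b/0.20) + Φ(−1.96 − b/0.20).

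| Assumed shift b (SD) | b/0.20 | False-positive rate |
|---|---|---|
| 0 | 0 | 5.0% |
| 0.1 | 0.5 | 7.9% |
| 0.2 | 1.0 | 17.0% |
| 0.3 | 1.5 | 32.3% |

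The shifts are assumptions; the documents give none. One illustration of how 0.2 SD could arise, also with assumed inputs: half the women have a trait worth 0.8 SD on the biomarker, and in one arm only they are three times as likely to be sampled. Their share there becomes (0.5 × 3)/(0.5 × 3 + 0.5) = 75% against 50%, and the bias is 0.25 × 0.8 = 0.20 SD.

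**3. Which comparisons are exposed?**
- Less exposed: urine choline as change from enrolment, and azithromycin effects as change from week 19, which is nominally before the first dose at week 20. A stable shift shows in the first sample and can be adjusted for.
- Most exposed: colostrum and cord blood, which have no earlier sample, and BEP against control. BEP starts at enrolment, so the week-19 sample is already on supplement.
- Unclear: the text places niacin samples at the same time point as the enrolment and 32-week bloods, while Table 2 marks weeks 19 and 32. Whether a niacin sample at enrolment exists depends on reconciling these.
- Not exposed: birth weight, anthropometry, and the haemoglobin, ferritin, vitamin D and pregnancy microsampling blood taken from all who agree.

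**The case against.** The strongest reply is that arm-dependent selection is possible but not shown. Home visits and counselling follow one stated schedule for all arms, so control women too are easier or harder to reach. If convenience acts alike in every arm, the contrast is unbiased and only generalisability is affected. Urine is due at enrolment, so women may be identified before any compliance is observed. These points stand. They reduce the likely size of the problem but do not supply the missing guarantee.

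The false-positive rates rest on assumed shifts and an unadjusted single-time comparison. That also stands: with no shift the rate is 5%, and paired samples help where the first precedes treatment.

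Four stronger readings are tempting and are not supported:
- A reader might infer that arm-aware field staff choose the women. No section says who approaches them or what that person knows.
- A reader might infer that supplemented arms are filtered for engagement and control is not. The common visit schedule argues against this.
- A reader might apply the 21% loss to the 50 dyads and conclude that the number is unattainable. That figure is a whole-trial allowance that includes pandemic-related missed birth assessments. It is not a retention rate for this group, and 50 can be read as a target.
- A reader might extend the point to imaging. The section says only "On a sub-sample of 50 infants per arm, brain imaging will be performed" and gives no selection method.

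It is also fair that the remedy comes late. Under Trial status, recruitment began in July 2019 and was due to end in January 2022, and specimens were added in August 2020. Many of these women may already have been chosen.

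**Conclusion.** The point holds as a weakness in a stated method. Comparability of the arms in the convenience sub-sample is not guaranteed, and comparisons between arms are what the sub-sample is for. The damage ranges from none (selection unrelated to arm) to a false-positive rate of about 8%, 17% or 32% for assumed shifts of 0.1, 0.2 or 0.3 SD, in an unadjusted two-sided 5% test with 50 per arm. It rests on two things: the inference that the arm was known when each quota was filled, and the absence of any described random or masked selection. The documents do not show that bias has occurred. The primary outcome is untouched, so this is an improvement the trial should make, not a threat to its main conclusion.

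**What to change.** For women not yet selected, have the independent statistician draw the sub-sample at random within arm from the randomisation list, with an ordered list of random replacements for refusals. The sample size does not change. The price is somewhat more refusals and travel. Access will still filter some specimens: cord blood is due within 30 minutes of birth at a site with no maternity home, so completion should be reported by arm.

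For women already picked by convenience:
- report numbers approached, refused and sampled by arm;
- compare sampled with unsampled women at baseline, by arm;
- adjust for baseline covariates, and for the pre-intervention sample where one exists;
- label these between-arm comparisons exploratory and not protected by randomisation.

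This reporting uses the trial's baseline data plus a log of approaches. If no such log was kept, the article should say so.

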### Interventions

In the control arm, standard of care, i.e., ANC care, nutritional counseling, health promotional messages of exclusive breastfeeding, and care for intrapartum and postnatal care will be disseminated to all pregnant women. In “Intervention arm 1,” in addition to the standard of care, 2 sachets of BEP supplements per day from enrolment till birth outcome will be allocated to each woman by a trained research team member at initial and subsequent follow-up visits. BEP is a certified product of the World Food Program and is locally produced by the Ismail Industries in Karachi. The manufacturers have no role in any part of the study. Each sachet contains a caloric value of 400 kcal per 75 g and approximately 10.5 g of protein. The sources of protein are mainly chickpea, peanuts, lentils, legumes, and skimmed milk. In “Intervention arm 2,” the same standard ANC counseling BEP interventional doses will be administered to each participant in addition to 2 prophylactic doses of azithromycin tablets 2 g orally at weeks 20 and 28 of gestation (window period of 7 days). In “Intervention arm 3” lastly, daily single doses of nicotinamide 100 mg orally and choline 450 mg orally will be dispensed to each pregnant woman in addition to the same standard of care plus BEP diet supplements. Provision of all ANC services as well as referral for any complication(s) during pregnancy and intrapartum period will be undertaken for all arms. Provision of all ANC services as well as referral for any complication(s) during pregnancy and intrapartum period will be undertaken for all arms. There will be no alternation to the usual care pathways (including use of any medication) and these will continue for all trial arms. All other non-study treatments, such as medications and supplements, will be recorded at each follow-up in all arms. In case any severe illness or adverse event is reported or observed, the intervention may be paused or stopped for a limited period after the investigators and the Data Safety and Monitoring Board are consulted.

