**Specimens’ collection during pregnancy**											
*Maternal hemoglobin level* ^*j*^	×								×		
*Maternal ferritin level* ^*j*^	×								×		
*Maternal vitamin D level* ^*j*^	×								×		
*Maternal VAM blood collection* ^*j*^	×								×		
*Maternal urine collection for Choline metabolites* ^*k*^	×								×		
*Maternal plasma collection for proteomics* ^*k*^								×	×		
*Maternal plasma collection for Niacin metabolites* ^*k*^								×	×		
*Maternal stool collection*											

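### The protocol names plasma as the specimen for erythrocyte NAD and NADP, but plasma contains no red cells; the text and Table 2 need a red-cell or whole-blood aliquot for the coenzymes

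*Protocol article*

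**What the plan says.** The section on maternal blood specimen collection describes a sub-study: "On a sub-sample of 50 pregnant women per arm approached via convenience sampling". In these women the article plans to collect "plasma for Niacin metabolites and for niacin co-enzymes, specifically erythrocyte nicotinamide adenine dinucleotide (NAD") together with NADP. The stated purpose is "to compare the levels of these metabolites among the four arms with those receiving an extra daily dose". The arm with the extra dose is intervention arm 3, which according to the Interventions section receives "daily single doses of nicotinamide 100 mg orally and choline 450 mg orally" on top of the supplement and standard care.

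In Table 2, the block on specimens during pregnancy has one row for this work: "Maternal plasma collection for Niacin metabolites". It does not mention the coenzymes. The only other maternal blood in the section has its own stated uses: hemoglobin, ferritin and vitamin D, and the microsampling specimens, of which the article says "Separate blood specimens for metabolomic analyses will be simultaneously drawn".

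**The concern.** The sentence fixes both a specimen and an analyte, and the two do not fit. An erythrocyte coenzyme sits inside the red cell; plasma is the fraction from which the cells have been removed. A team working only from this text and Table 2 has an instruction to collect plasma and none to keep red cells.

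The coenzymes are the only cellular measure of niacin status that the article names, and they are meant to show a contrast between arm 3 and the other arms. Without them, the niacin comparison in this sub-study would rest on the circulating metabolites alone. Red cells that were not kept cannot be recovered later from stored plasma, so the point is worth settling while any draws remain.

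**Working it through.** The protocol gives no figure to reproduce here. The check is to set the specimen and the analyte side by side and then look for any other source of red cells.

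1. **Text.** Specimen: plasma. Analytes: niacin metabolites, and coenzymes specified as erythrocyte NAD and NADP. A single noun, plasma, governs both purposes. It suits the metabolites but not the coenzymes.
2. **Table 2, pregnancy specimens.** The niacin row lists plasma, for metabolites. No row provides red cells, red-cell lysate or whole blood for the coenzymes. Taken alone the row is correct; it does not supply what the text lacks.
3. **Other maternal blood at these visits.** The blood for hemoglobin, ferritin and vitamin D has those uses. The microsampling specimens are assigned to metabolomics. The plasma for proteomics is again plasma. None is assigned to NAD or NADP.
4. **Other specimen sections.** Urine is for choline metabolites, and cord blood goes on dried blood spot cards. Stool, colostrum and infant blood also have their own stated purposes. None provides maternal red cells for the coenzymes.

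So nothing in the article repairs the mismatch.

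**Upper bound on reach.** Inputs: 50 women per arm and 4 arms (maternal blood section), and 2 draws per woman. The text ties the niacin sample to the timing of the main maternal blood draw, at enrollment and week 32. Table 2 as extracted appears to mark weeks 19 and 32, although its layout may be broken. Either reading gives two draws, and the timing difference plays no part in this point.

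- Women: 50 x 4 = 200.
- Draws: 200 x 2 = 400.

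The 400 is a ceiling. It assumes that every place in the sub-sample is filled, that every woman gives both samples, and that no red cells are kept.

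**Whether a correction can still help.** The protocol version table dates the addition of specimens to August 2020, and the Trial status section expects recruitment to finish in January 2022. Women enroll at 8 to 18.9 weeks, so the week-32 draw falls between 32 - 18.9 = 13.1 and 32 - 8 = 24 weeks after enrollment. Some week-32 draws could therefore fall after recruitment closes, if the sub-sample was still being filled at that stage. The article does not say whether it was.

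**The case against.** The strongest reply is that this is compressed grammar. The sentence itself specifies erythrocyte coenzymes, under a heading about maternal blood. A laboratory asked for an erythrocyte assay knows which fraction it needs, and a tube of anticoagulated blood that yields plasma also yields packed red cells. Processing steps belong in a laboratory manual or in the full protocol, neither of which is shown, and an article may leave them there. Table 2 uses short labels and is not a reliable list of everything collected: its maternal stool row, as extracted, carries no marks although the text schedules stool at weeks 19 and 32.

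Much of this stands. Loose wording is a plausible cause, and the laboratory may already keep the cells. What does not stand is that nothing needs correcting. The article did not leave the specimen to another document; it named one, and a laboratory manual would have to depart from the text to be right.

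A reader might go further and infer that all the erythrocyte NAD and NADP data are lost, or that 400 specimens are useless. The documents do not support that. They describe no centrifuging or discarding of cells, and the plasma would in any case still serve for the niacin metabolites. A reader might also infer that these coenzymes are the main evidence that nicotinamide was taken. That is too strong as well: the Follow-ups section makes a designated team responsible for daily administration, and the case report forms capture compliance with the interventions.

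**Conclusion.** The contradiction is real: as written, the erythrocyte coenzymes cannot be measured from the named specimen, and no other specimen in the article is assigned to them. It is a minor point. It concerns one secondary biomarker in a convenience sub-sample, with at most 400 planned draws involved, and for the coenzyme measure only. The niacin metabolites, the birth-weight outcome and the sample size are untouched.

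The conclusion rests on the ordinary meaning of plasma and on a reading of every specimen section and of Table 2. Whether any data are actually missing depends on what the laboratory kept, which the article does not show.

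**What to change.** In the maternal blood section, name two fractions from the same draw: plasma for niacin metabolites, and a retained red-cell or whole-blood aliquot for NAD and NADP. Make the same change in Table 2, either by extending the niacin row or by adding a row for the coenzymes.

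The sponsor should also confirm with the laboratory whether red cells were kept from draws already made. If they were, correcting the text and table is enough. Only where they were not should erythrocyte NAD and NADP be reported on the reduced number of women, with that denominator and the reason stated.

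The cost is one extra aliquot per draw, the freezer space for it, and a line in the laboratory instructions. No additional venepuncture is needed. The possible downside is that some earlier draws may have to be reported without this measure.
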